# The effect of primary delivery of the anterior compared with the posterior shoulder on perineal trauma: a study protocol for a randomized controlled trial

**DOI:** 10.1186/1745-6215-15-291

**Published:** 2014-07-21

**Keywords:** anal canal/injuries, delivery, obstetric/methods, delivery of the shoulders, labour stage, second, lacerations/prevention and control, obstetric labour complications/prevention and control, perineum/injuries

## Abstract

**Background:**

Approximately 85% of vaginal deliveries are accompanied by perineal trauma. The objective of this trial is to compare the incidence and degree of perineal trauma after primary delivery of the anterior compared with the posterior shoulder during vaginal birth. The hypothesis is that primary delivery of the posterior shoulder reduces the rate and degree of perineal trauma.

**Methods/design:**

This is a single-centre, randomized controlled trial, with computer-generated randomization in a 1:1 allocation ratio. Women planning their first vaginal delivery (*n* = 650) are randomized to primary delivery of either the anterior or posterior shoulder. The primary outcome is any perineal trauma. Additional outcomes are the perineal injury subtypes, postpartum bleeding, umbilical artery pH, Apgar score at 5 minutes and any neonatal birth trauma. Perineal trauma is assessed by a midwife or doctor blinded to the method of shoulder delivery. All midwives are trained in the two methods of shoulder delivery and in the grading of perineal tears. The trial is being undertaken at a Danish community hospital with 1,600 yearly deliveries. Data will be analyzed according to the intention-to-treat principle. Recruitment started in January 2013 and the trial is planned to proceed for 24 months.

**Discussion:**

Most delivery assistance techniques are based on tradition and heritage and lack objective evidence. This trial provides an example of how vaginal delivery techniques can be evaluated in a randomized controlled trial. The results of this trial will clarify the role that delivery of the shoulders has on perineal trauma and thereby provide knowledge to recommendations on birthing technique.

**Trial registration:**

ClinicalTrials.gov: NCT01937546.

## Background

Approximately 85% of vaginal deliveries are accompanied by trauma to the genital tract, with a higher risk at the first compared with subsequent vaginal births [1,2]. Among primipara with vaginal deliveries, 86% sustain a vaginal or perineal tear, and 77% require suturing of a lesion [1,3].

Birth trauma is associated with both short- and long-term morbidity, including pain, discomfort, dyspareunia and fecal incontinence, and perineal trauma may cause social problems and affect the psychological well-being of the mother [1,4]. The level of postpartum morbidity is related to the degree of trauma [5,6], and studies of preventive measures are therefore of interest.

Genital tract traumas are classified into subtypes according to the location and severity of the lesion. Most studies have evaluated the risk factors for third- and fourth-degree perineal tears that include the anal sphincter complex, so-called obstetric anal sphincter injuries (OASIS). Predisposing factors are increasing maternal age, heavier birthweight, longer duration of the second stage of labour, oxytocin augmentation, occiput posterior position and instrumental delivery [7-9]. The risk increases with the number of different risk factors [9]. Protective factors are previous vaginal delivery, epidural analgesia and multiparity [7-9]. Several perineal management techniques used during delivery have been studied, and a recent Cochrane review concluded that warm compresses and perineal massage seem to reduce the risk of OASIS [4]. The introduction of an interventional perineal protection programme also seems to reduce the incidence of OASIS [10-12].

Leading textbooks recommend primary delivery of the anterior shoulder by gentle traction if the shoulders are not delivered spontaneously [13,14]. However, if shoulder dystocia occurs, the recommended manoeuvres are primary delivery of the posterior arm or primary delivery of the posterior shoulder, with the woman positioned on her hands and knees (Gaskin’s manoeuvre) [15,16]. A computer-simulated trial of the manoeuvres used during shoulder dystocia found that primary delivery of the posterior arm caused an 80% reduction in the delivery force and a 70% reduction in stretch to the brachial plexus [17]. Primary delivery of the posterior shoulder could therefore be of advantage during uncomplicated deliveries, but, to the knowledge of the authors, various methods of shoulder delivery have never been studied previously.

The objective of this trial is to evaluate the incidence and degree of perineal trauma after primary delivery of the anterior shoulder compared with primary delivery of the posterior shoulder during vaginal birth in primiparous women in a randomized controlled trial. The hypothesis is that primary delivery of the posterior shoulder reduces the rate and degree of perineal trauma.

## Methods/design

### Setting

This is a single-centre, prospective, investigator-initiated, randomized controlled trial. The trial is being undertaken at the University of Copenhagen, Holbæk Hospital, which is a Danish community hospital with an obstetric unit with 1,600 yearly deliveries. Recruitment started 1 January 2013, and the trial is planned to proceed for 24 months.

### Participants

Eligible participants are primiparous women and women with one previous Cesarean section, who are planning a vaginal delivery of a fetus in cephalic presentation. Patients have to be able to provide informed oral and written consent. Exclusion criteria are multiparity with a previous vaginal delivery, multiple pregnancy, acute or planned Cesarean section, delivery before 35 weeks of gestation, and breech delivery.

### Interventions

The trial interventions take place during vaginal birth after the delivery of the head. The head is supported in the spontaneous rotation that occurs after its delivery, and the shoulders are delivered according to randomization. The intervention is primary delivery of either the anterior or the posterior shoulder, as illustrated in Figure 1 and the additional movie files (see Additional file 1 and Additional file 2). It is performed by the midwife placing her hands around the head of the baby and applying gentle traction in the appropriate direction.

**Figure 1 F1:**
[figure not shown]
Primary delivery of (A) anterior shoulder and (B) posterior shoulder.

All midwives are trained in the two interventions by the primary investigator (HW) to secure uniform use of the techniques. Training sessions include an introductory video of the two methods and practical training on a birthing phantom (MODEL-med ‘Sophie and her Mum Full Birth Obstetric Trainer’, Carnegie, Australia). All midwives are also trained in evaluation and classification of perineal tears using an e-learning programme (GynZone ApS, Aarhus, Denmark). Primary training sessions (*n* = 14) took place from February to November 2013, and additional sessions are held every second month during the course of the trial to train new midwives and update previously trained midwives. Attendance at a training session accredits midwifes to deliver included patients.

The participants can deliver in the position they prefer, and if spontaneous delivery of the shoulders occurs, this is to be respected regardless of randomization. If during delivery the midwife judges that an alternative method of delivery is preferred with regard to the safety of the birthing mother, this overrules randomization. Episiotomy may be used in accordance to local guidelines, as judged necessary by the midwife. In case of vacuum-assisted delivery, which according to guidelines is performed by physicians, the midwife delivers the shoulders. Any deviations from the protocol are registered on the clinical registration form.

### Outcomes

The primary outcome is any perineal trauma. Secondary outcomes are the perineal injury subtypes, postpartum bleeding in millilitres evaluated 2 hours after birth, umbilical artery pH, Apgar scores at 5 minutes and neonatal birth trauma, including fractures of the clavicle and humerus, and brachial plexus injury.

Perineal traumas are classified as anterior or posterior, and posterior traumas are classified into subtypes. Anterior trauma comprises lacerations of the labia that do or do not require suturing. Posterior subtypes comprise lacerations of the vagina and/or perineum that do not require suturing; first-degree tears, where only the skin or mucosa is involved (1A: <1.5 cm; 1B: ≥1.5 cm); second-degree tears, where skin and perineal muscle is involved with the anal sphincter intact but not visible (2A) or visible (2B); third-degree tears involving the anal sphincter complex (3A, less than 50% of the external anal sphincter is torn; 3B, 50% or more of the external anal sphincter is torn; 3C, both the internal and external anal sphincters are torn); and fourth-degree tears involving the anal sphincter complex as well as anal epithelium [18,19].

### Assessment

After delivery of the placenta, a blinded midwife or doctor not otherwise involved in the delivery assesses the perineum and grades the perineal tears. Tears are sutured and officially classified and coded independently of the trial by the midwife responsible for the delivery or a doctor according to the hospital guidelines. Secondary outcome measures are registered by the midwife responsible for the delivery. Assessors of the primary outcome and the primary investigator are blinded to randomization.

Registered third- and fourth-degree tears are validated through manual assessment of patient records. We assume that higher-degree tears, in particular, may be diagnosed after trial assessment during repair. In order not to underestimate the level of higher-degree tears, data on all third- and fourth-degree tears in our study population registered in the hospital register during the trial period will be retrieved after the end of the trial. These data will be validated against patient records and any additional confirmed cases of third- or fourth-degree tears in our study population will be incorporated into the final dataset.

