### Randomization

Randomization is computer-generated, with a 1:1 allocation to primary delivery of the anterior or posterior shoulder by a third party not otherwise involved in the trial. The allocation is concealed in 650 identical, opaque, sequentially numbered sealed envelopes. The allocation list is stored electronically by a third party not otherwise involved in the trial. Recruited women are randomized after confirmation of consent upon arrival at the delivery ward and a random allocation envelope is drawn. The envelope is opened by the midwife when the patient enters the second stage of labour and is destroyed thereafter. The allocation is only shown to the midwife and the assistant, and if necessary the obstetrician. During delivery, the midwife and assistant observe what shoulder is delivered first, and this is registered on the clinical registration form.

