### Data management

Data are recorded on clinical registration forms and entered into a SPSS database (SPSS Inc., Chicago, IL, USA) by the primary investigator. Data will be available only to the investigators and the data monitor. After completed follow-up, data will be cleaned and consecutively locked before the allocation is broken.

All clinical registration forms are identified by a coded ID number according to randomization, to maintain participant confidentiality. All study-related participant information is stored in a locked room at the study site. Lists linking participant ID numbers to personal identification numbers are stored separately. Trial data will be stored for 10 years. Data will subsequently be anonymized and personally identifiable information destroyed.

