### Data monitoring

The steering committee consists of the authors of the protocol and [name], Head Midwife, Department of Obstetrics and Gynaecology, University of Copenhagen, Holbæk Hospital.

To ensure that it is not unethical to continue due to one intervention causing markedly more perineal trauma, interim analyses will be performed by a data monitor not otherwise involved in the trial after the first year and consecutively every 6 months until the end of the trial. In the interim analysis, the distribution of the two interventions will be estimated among cases with no perineal tears and cases with third- and fourth-degree tears. The steering committee will be notified if more than 60% of the cases with no tears or a higher-degree tear belong to a particular intervention group. The steering committee will then decide if the trial has to be stopped before completion.

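### The primary investigator is declared blinded but enters the forms that record which shoulder was delivered first and any deviations, so most allocations can be inferred before database lock

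*Protocol article*

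**What the plan says.** The claim of blinding is in the Assessment section of the protocol article: "Assessors of the primary outcome and the primary investigator are blinded to randomization". Two other statements support the intention. Under Randomization, the people allowed to see the allocation are the midwife, the assistant and, where needed, the obstetrician; the primary investigator is not among them. Under Data management, cleaning and locking come before the allocation is broken.

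Three further statements describe what the investigator handles:

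- Randomization: "the midwife and assistant observe what shoulder is delivered first, and this is registered on the clinical registration form".
- Interventions (text after Figure 1): "Any deviations from the protocol are registered on the clinical registration form".
- Under Data management, on who enters these forms: "Data are recorded on clinical registration forms and entered into a SPSS database (SPSS Inc., Chicago, IL, USA) by the primary investigator".

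The article describes no split form, no masked field and no second person for data entry. The Statistics section plans a per-protocol and an as-treated analysis, so both the shoulder delivered and adherence to allocation have to be in the dataset at some point.

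**The concern.** The intervention in this trial is the shoulder order itself. A form that shows which shoulder came first shows the treatment received, and a note of any departure from allocation turns that into the treatment assigned. Whoever enters such forms can infer the arm without seeing the allocation list. Holding that list back until lock then withholds little that the person at the keyboard does not already have.

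Two things are at stake. First, decisions made before lock, such as resolving unclear entries and raising queries, could be made with the probable arm in view. The same holds for confirming third- and fourth-degree tears against patient records and adding cases found in the hospital register, if the investigator does that work. Second, the trial report would claim a safeguard that the protocol's own data flow removes.

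**Working it through.** **Plan's own figure.** The document gives no figure on blinding, so there is none to reproduce. Its sample size of 250 per arm (85% against 75%, 80% power, 0.05, taken as two-sided) does reproduce with the usual two-proportion formula with pooled variance. It plays no part here, and nothing in this point changes it.

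**Step 1: compare the statements.**

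| Item | Where stated | Seen by the primary investigator? |
|---|---|---|
| Allocation list | Randomization: held by a third party | No |
| Allocation envelope | Randomization: opened by the midwife, then destroyed | No |
| Shoulder delivered first | Randomization: on the clinical registration form | Yes, at entry |
| Protocol deviations | Interventions: on the clinical registration form | Yes, at entry |
| Entry of the forms | Data management: by the primary investigator | Yes |

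The same name is used for the form in all three sections, and one role is named for entering it.

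**Step 2: what can be inferred.** Take the simple rule: with no departure logged, guess that the allocation equals the shoulder delivered; with a departure logged, guess the other arm. Let *a* be the share of births in which the allocated shoulder came first, and *f* the share of the remaining births in which the departure is logged. Assume a logged deviation says that it concerns shoulder order. Then:

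share of allocations inferred correctly = a + (1 − a) × f

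The document gives neither *a* nor *f*, so both are assumed over a range:

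| Adherence *a* | f = 0 (shoulder order alone) | f = 0.5 | f = 0.9 | f = 1 |
|---|---|---|---|---|
| 0.70 | 70% | 85% | 97% | 100% |
| 0.80 | 80% | 90% | 98% | 100% |
| 0.90 | 90% | 95% | 99% | 100% |
| 0.95 | 95% | 97.5% | 99.5% | 100% |

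Worked example: a = 0.80 and f = 0.9 give 0.80 + 0.20 × 0.9 = 0.98. With 1:1 allocation, a guess without information is right about 50% of the time. Shoulder order alone would fall to that level only if adherence were itself 50%; even then, f = 0.9 would give 0.50 + 0.50 × 0.9 = 95%.

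**Step 3: number of forms.** Applying the 18% acute Cesarean rate in the Statistics section, 650 × 0.82 = 533 vaginal births, before any other drop-out. From shoulder order alone, 533 × 0.70 = 373 to 533 × 0.95 = 506 allocations would be inferred correctly, against about 267 by chance.

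**Step 4: where this could act.** The first grading of the tear is made by someone else, who is blinded. What follows is data entry (assigned to the primary investigator), cleaning (no one named), and the validation and later addition of third- and fourth-degree tears (no one named). Moving a tear between second and third degree does not change the primary outcome of any perineal trauma. Adding a register case changes it only for a woman graded as having no tear. The exposure is therefore mainly in the injury subtypes, which are secondary outcomes.

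**The case against.** The best defence is that the primary investigator's blinding is a secondary safeguard and that those that matter most are intact. The primary outcome is graded by a blinded midwife or doctor who took no other part in the delivery, the allocation is concealed, the main analysis follows intention to treat, and higher-degree tears are checked against patient records. All of this stands, and it limits the severity.

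It is also fair that the form is described as holding the shoulder delivered and deviations, not the allocation. The protocol accepts spontaneous delivery of the shoulders whatever the allocation, so a spontaneous birth against allocation may count as following the protocol and go unlogged. Inference is then strong but not certain. This also stands; it moves the result within the table above and does not bring it back to 50% at the assumed adherence.

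Several stronger readings are tempting, but the document does not support them:

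- *That the tear assessors are unblinded too.* They share the sentence with the primary investigator, but they are separate staff, and nothing says they see a sheet showing shoulder order.
- *That the investigators watch the results throughout the trial.* The article limits who may see the data but gives no timing.
- *That the interim rule tells the authors which arm is ahead.* It does say "The steering committee consists of the authors of the protocol", together with the head midwife, and that the committee is notified when the 60% mark is passed. It does not say that the arm is named, and coded labels are not ruled out. How often that rule fires is a question about the threshold and does not measure this problem.
- *That midwife training is biased.* The primary investigator trains the midwives, but nothing in the text shows that knowledge of results reaches the sessions.

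**Conclusion.** The contradiction is real and lies within the article: the primary investigator is stated to be blinded, and the described data flow lets that person infer most allocations before lock. The size is about 70% to 95% from shoulder order alone at an assumed adherence of 70% to 95%, and close to 100% if every departure from allocation is logged. This rests on adherence and logging rates that the document does not give, and on the form being entered as a whole by the named person, which is what the text says.

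The conclusion is limited to the primary investigator. It does not mean that the trial's blinding fails as a whole, and it does not show bias in the primary outcome. The exposure is in data entry, in cleaning, and in the validation and addition of third- and fourth-degree tears, the last two only if the investigator takes part. It should be fixed, but it does not put the main comparison in doubt.

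**What to change.** Preferred: put shoulder order and deviations on a separate sheet that goes directly to the third party who already keeps the allocation list. Merge it with the outcome data only after tear validation is finished and the database is locked. Carry out the validation and addition of third- and fourth-degree tears without sight of shoulder order, and state who does it.

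If this is not done, remove the primary investigator from the blinding statement in the Assessment section and report that role as not blinded.

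The cost is small: one form becomes two, and one line of the data flow changes. The third party already exists, so no extra staff are needed. The drawback is that deviations enter the database later. The second option costs only a change of wording, but it leaves the exposure in place.

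### The final third- and fourth-degree tear outcome mixes the blinded grade with cases added from hospital records that may be made by someone who knows the allocation

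*Protocol article*

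**What the plan says.** The Outcomes section of the protocol article sets a single primary outcome, "The primary outcome is any perineal trauma", and then lists the secondary ones: "Secondary outcomes are the perineal injury subtypes", followed by bleeding, umbilical artery pH, Apgar score and neonatal birth trauma.

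The Assessment section describes three routes by which information on tears arises:

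- **Trial grading.** After the placenta is delivered, "a blinded midwife or doctor not otherwise involved in the delivery assesses the perineum and grades the perineal tears".
- **Routine coding.** Tears are also sutured and "officially classified and coded independently of the trial by the midwife responsible for the delivery or a doctor".
- **Record checks.** Severe tears already registered are validated against patient records. When the trial has finished, the hospital register is searched for all third- and fourth-degree tears in the study population, these are checked against records, and "any additional confirmed cases of third- or fourth-degree tears in our study population will be incorporated into the final dataset". The stated reason is that such tears may be recognised only during repair.

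On blinding, the same section says "Assessors of the primary outcome and the primary investigator are blinded to randomization", and on registration it says "Secondary outcome measures are registered by the midwife responsible for the delivery". The abstract is broader: "Perineal trauma is assessed by a midwife or doctor blinded to the method of shoulder delivery".

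**The concern.** The blinded assessor's grade is not the last word on severe tears. Cases can enter the final dataset through routine coding and notes, and under the Randomization section the delivering midwife opens the envelope and observes which shoulder comes first. If severe tears were looked for, referred or coded more readily in one arm, the difference would pass into this outcome. The register search retrieves only third- and fourth-degree tears, so that step can add cases but cannot reveal tears that the assessor over-graded.

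The outcome is secondary but not peripheral. The hypothesis concerns how severe the trauma is as well as how often it occurs, and these are its most serious grades.

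There is also a conflict within the text. If secondary outcomes are registered by the delivering midwife and tear subtypes are secondary outcomes, then someone who knows the allocation registers the grade that a blinded assessor is said to give.

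**Working it through.** **1. The plan's own figure, and whether this point touches it.** Inputs from the Statistics section: 85% against 75%, 80% power, significance level 0.05 (taken as two-sided), mean proportion 0.80.

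n per arm = [1.960·√(2·0.80·0.20) + 0.8416·√(0.85·0.15 + 0.75·0.25)]² / 0.10² = (1.1087 + 0.4723)² / 0.01 = 249.96, rounded up to 250.

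This reproduces the stated 250. It concerns any trauma. A tear moved up to third or fourth degree changes that count only if the blinded assessor had recorded no trauma at all, so the primary outcome is hardly affected.

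**2. Timing against the interim rule.** The Data monitoring section places interim looks after the first year and then half-yearly until the trial ends. The register is searched only after that, so cases added from it cannot enter the counts to which the 60% rule applies.

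**3. Who supplies what, and what they know.**

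| Source | Made by | Knows the allocation? |
|---|---|---|
| Trial grade | Independent midwife or doctor | No |
| Hospital code | Delivering midwife, or a doctor | Midwife yes; an obstetrician only where needed (Randomization) |
| Record validation | Not stated | Not stated |
| Registration of secondary outcomes | Delivering midwife | Yes |

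Checking a code against the notes can show that the two agree. It cannot restore blinding if both were written by the same person.

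**4. Possible size.** The protocol gives no severe-tear rate, so the following inputs are assumptions: the same true rate p = 3–8% in both arms; the blinded assessor finds a share s = 60–90% of severe tears; records recover a share r of those missed. Vaginal births per arm: 650 × (1 − 0.18) / 2 = 266.5, taken as 266.

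Observed rate = p·[s + (1 − s)·r].

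- Worked case, p = 5%, s = 80%. With r = 90% the rate is 0.05 × 0.98 = 0.049 (13.0 women); with r = 60% it is 0.05 × 0.92 = 0.046 (12.2 women). OR = (0.046/0.954) / (0.049/0.951) = 0.94.
- r equal in both arms (90% and 90%): OR = 1.00 throughout.
- r = 90% against 60%: OR from 0.87 to 0.97 over the whole range.
- r = 100% against 50%: OR from 0.79 to 0.95. The extreme is p = 8%, s = 60%, with 21.3 against 17.0 women.

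A second parametrisation, also assumed, adds cases as a percentage of the blinded count. An addition of 30% against 10% gives a risk ratio of 1.30/1.10 = 1.18; 40% against 10% gives 1.40/1.10 = 1.27. With a blinded rate of 4–8% (10.6 to 21.3 women per arm), the excess runs from 0.20 × 10.6 = 2.1 to 0.30 × 21.3 = 6.4 women.

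For scale, 13 events per arm give a standard error of the log odds ratio of √[2·(1/13 + 1/253)] = 0.40, so an odds ratio of 1.00 would carry a 95% interval of about 0.45 to 2.2.

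**The case against.** The strongest case on the other side is that the register step is disclosed, has a sound reason and avoids under-counting severe tears. Methods claim blinding only for assessors of the primary outcome and for the primary investigator, and severe tears are secondary. Data are cleaned and locked before the allocation is broken. The sentence on secondary outcomes can be read as covering only the non-perineal ones. A separate variable and a rule for disagreements are the kind of detail that a fuller protocol or analysis plan may hold.

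Much of this stands, and it rules out several stronger readings that a reader might infer:

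- *That records correct severe tears only upwards.* This is true of the register search. But severe tears already registered are also validated, and the Discussion says that all those in the final analysis will be, so a case could be removed. What happens to unconfirmed cases is not stated.
- *That every record comes from an unblinded person.* A coding doctor may not know the allocation.
- *That added cases could push the interim analysis towards its 60% threshold.* The timing excludes this.
- *That Methods promise blinded severe-tear grading in the final dataset.* The unqualified statement is in the abstract.

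What the objection does not remove is the stated rule itself, which merges two kinds of ascertainment. A late lock cannot take bias out of a source code. The lock is also limited protection if the primary investigator does the validation: that person enters the registration forms (Data management), which record the first-delivered shoulder and any deviations, so the allocation could often be inferred. The narrow reading of the registration sentence is plausible, but the text does not say it.

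**Conclusion.** The point holds for the final third- and fourth-degree tear outcome. That outcome is a composite of a blinded grade and record-derived cases that may originate with the delivering midwife, and the abstract's blinding sentence does not describe it. The Assessment section also needs reconciling on who registers tear subtypes.

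The size of any bias is unknown. It is zero if coding does not depend on arm, and the document gives no evidence that it does. If recovery differed by arm, the assumed range gives odds ratios of 0.79 to 0.97 with no true effect. This is small against the sampling error for so rare an outcome, but unlike sampling error it could not be detected from the merged data. The primary outcome and the sample size are essentially untouched, and so is the interim rule as far as the register step goes. The change is worth making because it is cheap, not because a large distortion has been shown.

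**What to change.** - Keep the blinded assessor's grade as its own variable, which record checks cannot overwrite.
- Report severe tears twice: by blinded grade alone, and with record-confirmed cases added. Show cases added and removed by arm. This also settles which source prevails in each analysis.
- Have the record validation done before database lock by someone who sees neither the allocation nor the first-delivered shoulder.
- Reword the Assessment section so that the delivering midwife registers only the secondary outcomes other than tear grade.
- Qualify the abstract: the trial grading is blinded, while severe tears are supplemented from hospital records.

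The cost is wording, one variable, one additional analysis and a suitably masked person for the record check. The downside is that two severe-tear figures are reported, and the blinded-only one may miss tears found at repair. For that reason neither figure should stand alone.
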